Many factors determine whether patients experience postoperative pain, including the type of intervention, the presence of complications, patient age, and individual tolerance. In particular, the type of mesh fixation employed for the hernioplasty has a strong influence on postoperative pain
[16,17]. In a recent review, mesh fixation with glue was compared to mesh fixation with staples for an endoscopic inguinal hernia repair
[18]. For the TAPP repair, two randomized controlled trials
[19,20], one non-randomized trial
[21], and two case series
[22,23] were reviewed. The authors of the review found less postoperative pain and more rapid recovery after glue fixation than after staple fixation, without any significant difference in the recurrence rate. Nevertheless, the authors concluded that, due to the overall poor quality of the currently published data, future well-designed studies are required to demonstrate the superiority of fibrin glue over mechanical stapling for mesh fixation. Thus, well-designed, randomized studies that compare glue and staple fixations for TAPP repair remain warranted. Most previous studies applied only one mesh fixation method for patients with bilateral hernias. Only one study compared glue and staple fixations in single patients with bilateral hernias
[24]; interestingly, that study was not included in the review by Schäfer et al.
[18].

This study protocol describes a two-by-two trial design that will be used to compare the two fixation methods in two groups of randomized patients; one group with unilateral hernias and the other group with bilateral hernias. The latter group will allow a comparison of the two methods in a single patient. This design will eliminate the inter-individual bias that may influence the unilateral hernia group. This study focuses on early postoperative pain, particularly during the first two postoperative days. In many other studies, pain is first measured one month after surgery.

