	• Re-operation, defined as the need for re-operation during the initial hospital stay
	• Bleeding
	• Urinary retention, urinary tract infection
	• Pulmonary infection
	• Any serious deviation from the normal postoperative course
Time to return to normal activities	Time, in days, from hospital discharge to first working day
Relapse	Within 1 year of surgery
Economic impact	Calculated based on the following factors:
	• Cost for glue, staples, and instruments to apply glue or staples
	• If relevant: cost for excess operating time for the “slower” mesh fixation
	• Length of hospital stay (cost/day)
	• Medical leave of absence (converted into a monetary amount based on an average salary)

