### Trial interventions

Patients will be randomized according to the following scheme:

Primary arm 1: Patients with a unilateral inguinal hernia

secondary arm 1: mesh fixation with tissue glue

secondary arm 2: mesh fixation with staples

Primary arm 2: Patients with bilateral inguinal hernias

secondary arm 1: right side, tissue glue; left side, staples

secondary arm 2: right side, staples; left side, tissue glue

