### Sample size calculation

The sample size was calculated under the hypothesis that either glue fixation or staple fixation is superior for the primary endpoint (= pain after 24 h)(two-sided analysis). Lovisetto reported a mean VAS pain score of 1.9 for glue fixation and 2.6 for staple fixation one month after TAPP repair
[19]. The observed difference of 0.7 is usually considered to be of no clinical relevance. We thus assumed a difference of 1 as a clinically relevant difference. Standard deviation was estimated to be equal 1, resulting in a standardized effect size of 1 which generally is considered clinically relevant. The sample size calculation was performed as two-sided analysis with a type I error of α = 0.05 and a power of (1-β) = 0.90.

Based on these assumptions, we calculated that 23 patients per arm would be required for unilateral hernias (t-test for two independent samples with common variance). Assuming a drop-out rate of 20%, the total number of patients needed per arm is 29, resulting in a total of 58 patients with unilateral hernias. For the second arm with bilateral hernias we calculated that 19 patients would be required (t-test for paired samples), assuming an intra-individual correlation of 0.2 (derived from a preliminary, unpublished analysis of patients with bilateral inguinal hernias that had undergone a Lichtenstein procedure). With a drop-out rate of 20%, a total of 24 patients with bilateral hernias would be required, resulting in a total of 82 patients for the entire study.

With an annual case load of approximately 100 in the previous years, we estimate that patient recruitment should be achieved within one or two years.

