### Statistical analysis

The statistical analysis will be performed with SPSS Statistics for Windows (IBM Corp., Armornk, NY, USA). A two-sided p-value <0.05 will be considered statistically significant. Descriptive statistics will be used to analyze the baseline characteristics. For the superiority analysis of pain intensity at 24 h after surgery, the Mann−Whitney U and Wilcoxon tests will be applied, as appropriate. To adjust for multiple testing, the Hochberg procedure will be applied
[29].

Pain measurements performed at 4, 8, 12, 24, 36, 48 h after surgery by patients with unilateral and bilateral hernias will be analyzed in one mixed model to assess the mean ranks of the NRS scores with adjustments for time, treatment, and unilateral versus bilateral hernias. To compare other continuous secondary endpoints (e.g., operating time, length of hospital stay, postoperative administered analgesics, time to return to normal activity, and economic impact), the Mann−Whitney U and Wilcoxon tests will be applied, as appropriate. Chi-square statistics will be used to compare categorical secondary endpoints (e.g., incidence of chronic pain, rate of recurrence, and postoperative morbidity). Auxiliary, non-confirmatory analyses will be performed to assess the influences of baseline patient characteristics and treatment characteristics on the primary and secondary outcomes.

Intermittent missing values will be replaced by linear interpolation (e.g. post-operative pain values within 48 h after surgery). No interim analysis is planned for this study. Data from patients withdrawn from the study will be disregarded, unless exclusion is based on a postoperative patient request, and the patient agrees to the use of existing documented data.

The confirmatory analysis will be performed based on an intention-to-treat (ITT) design, and it will adhere to ITT principles. When a protocol violation occurs, a per protocol analysis (PP) will be performed for comparison.

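### Minor: only chi-square is named for categorical secondary endpoints, which overlooks the paired groins of bilateral patients and says little about 1-year relapse if it is rare

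*Protocol article*

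**What the plan says.** For categorical secondary endpoints, the Statistical analysis section of the protocol article names one method: "Chi-square statistics will be used to compare categorical secondary endpoints (e.g., incidence of chronic pain, rate of recurrence, and postoperative morbidity". The criterion is general: "A two-sided p-value <0.05 will be considered statistically significant". For continuous secondary endpoints, the sentence just before names an unpaired and a paired test and ends "Wilcoxon tests will be applied, as appropriate". The categorical sentence has neither a paired test nor that qualifier.

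The design has two cohorts. For unilateral hernias, Sample size calculation says "the total number of patients needed per arm is 29, resulting in a total of 58 patients with unilateral hernias". For bilateral hernias, "a total of 24 patients with bilateral hernias would be required". Trial interventions gives every bilateral patient both fixations, for example "secondary arm 1: right side, tissue glue; left side, staples". Table 1 defines persistent pain by nerve symptoms in the inguinal area on the same side, and gives relapse the window "Within 1 year of surgery". Both can therefore be recorded per groin. No expected relapse rate appears anywhere.

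**The concern.** There are two separate problems.

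**Pairing.** In the bilateral cohort, glue and staples are compared within the same man. A two-sample chi-square on 24 glue sides against 24 staple sides treats 48 groins as independent. If a man's two groins tend to share the outcome, the test uses too large a variance and loses sensitivity. The within-patient comparison is what the article presents as the strength of this cohort, and the article applies it to pain. Chronic pain is named in the chi-square sentence and may be commoner than relapse, so pairing probably matters most there.

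**Sparse relapse data.** Relapse is the listed endpoint that shows whether the mesh held, so readers will set it beside any pain benefit. The background section reports earlier evidence in that way: less pain with glue, "without any significant difference in the recurrence rate". In a trial sized for pain, a rare relapse endpoint gives either no test statistic or a p-value that does not show how large an excess is still compatible with the data.

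**Working it through.** **Inputs from the protocol article.** 29 per arm unilateral (58 in total), 23 per arm after the planned 20% drop-out; 24 bilateral patients, 19 after drop-out; two-sided 0.05; within-patient correlation 0.2, which the plan gives for pain only.

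**Assumptions (not in the documents).** Relapse 1% to 5% per groin; a 20% event rate to illustrate chronic pain; within-patient correlation 0.2 or 0.5 for binary outcomes.

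**The plan's own figures.** A two-sample t-test with standardized effect 1 needs 23 per arm (power 0.912), and 23/0.8 gives 29. A paired t-test with SD of the difference √(2 × (1 − 0.2)) = 1.265 needs 19 (power 0.903), and 19/0.8 gives 24. The total of 82 reproduces.

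**1. Chi-square on paired sides.** With event rate p and correlation ρ, the difference between two sides has variance 2p(1−p)(1−ρ)/n. The two-sample chi-square uses 2p(1−p)/n. Its approximate type I error is therefore 2 × [1 − Φ(1.96/√(1−ρ))]:
- ρ = 0.2: 1.96/0.894 = 2.19, about 2.8%
- ρ = 0.5: 1.96/0.707 = 2.77, about 0.6%

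For 24 pairs at a 20% event rate, direct calculation (uncorrected Pearson) gives:

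| Correlation | Type I error |
|---|---|
| 0 | 5.3% |
| 0.2 | 3.2% |
| 0.5 | 0.8% |

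The test is conservative.

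**2. Probability that nobody relapses (unilateral).** Without a relapse, chi-square does not exist. The probability is (1−p)^58, or (1−p)^46 for completers:

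| Assumed rate | 58 patients | 46 patients |
|---|---|---|
| 1% | 56% | 63% |
| 2% | 31% | 39% |
| 3% | 17% | 25% |
| 5% | 5% | 9% |

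**3. What remains possible with no relapses.** The Wilson upper limit for 0/n is z²/(n + z²), with z² = 3.84. At 0 v 0, the Newcombe interval for the difference is plus or minus that value. The paired Newcombe and Tango intervals give the same:
- Unilateral, n = 29: 3.84/32.84 = ±11.7 points; n = 23: 3.84/26.84 = ±14.3
- Bilateral, n = 24: 3.84/27.84 = ±13.8; n = 19: 3.84/22.84 = ±16.8

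**4. Effect of pairing on the interval (24 bilateral patients).**
- 1 both-sided and 2 glue-only relapses: −8% to +26% paired, −10% to +27% unpaired. This is a small change.
- 2 both-sided and 5 glue-only events (7/24 = 29% v 2/24 = 8%, nearer to a chronic-pain scenario): +2% to +40% paired, −2% to +42% unpaired.

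**5. Agreement of interval and p-value.**
- Bilateral, the second example above: the paired interval excludes zero. McNemar gives p = 0.025 uncorrected but 0.0625 exact; the unpaired Pearson gives 0.064.
- Unilateral, 4 v 0 of 29: interval −0.5% to +30.6%, Pearson p = 0.038, Fisher p = 0.112.
- Unilateral, 5 v 0 of 29: Fisher p = 0.052. The Wilson lower limit for 5/29 is 0.076, so the Newcombe lower limit is 0.172 − √((0.172 − 0.076)² + 0.117²) = +2%.

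**The case against.** The strongest reply is that this is one sentence in a journal article, with examples. Sparse-cell handling, effect estimates and intervals are commonly left to the full protocol or analysis plan, and nothing rules them out here. Chi-square statistics can loosely include McNemar's test, and the authors plainly recognise pairing: they use a paired t-test for sample size and name Wilcoxon for continuous endpoints. The rarity premise is also an assumption, and at 5% the chi-square would seldom be undefined. Finally, an interval adds no power. The sample size was set for pain, and 0/29 v 0/29 already looks uninformative.

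Much of this stands. The missing interval alone would not be a finding, the paired test may have been intended, and pairing changes little for rare relapse. What remains is that the text does fix a method, names recurrence and chronic pain under it, and gives no paired option where the adjacent sentence does.

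Three stronger readings are tempting but unsupported:
- A reader might infer false positives from ignoring pairing. With positive correlation the test is conservative.
- A reader might infer a plan to claim equal recurrence. The article plans none, and the background phrase describes a previous review.
- A reader might take near-certain non-significance under equal true rates as a defect. Any valid 5% test behaves that way.

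**Conclusion.** The point holds as a minor one. Taken literally, the named method is unpaired for side-specific endpoints in a cohort built on within-patient comparison. The cost is sensitivity: type I error of about 3% or under 1% instead of 5%, for 24 pairs, a 20% event rate and correlations of 0.2 and 0.5. For unilateral relapse with 29 per arm, the test is undefined with probability 17% to 56% if the rate is 3% down to 1%. This falls to about 5% if the rate is 5%, so the sparse-data part depends on relapse being rare. With no relapses, differences of about ±12 to ±17 points remain open, depending on cohort and drop-out. These event rates are assumptions, as is carrying the pain correlation of 0.2 over to binary outcomes. The primary pain analysis and the sample size are unaffected.

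**What to change.** In Statistical analysis, take chronic pain and recurrence out of the general chi-square sentence and state:

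*Side-specific categorical endpoints (chronic pain and relapse) will be reported as counts per fixation and as a glue-minus-staples risk difference. The unilateral cohort will use a Newcombe score 95% confidence interval, and the bilateral cohort a paired Newcombe or Tango score 95% confidence interval. The interval is the main result. Any p-value is supplementary: chi-square (Fisher's exact test if sparse) in the unilateral cohort and a McNemar-type test in the bilateral cohort.*

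The interval must be of score type, because a Wald interval has zero width at 0 v 0. One paired interval and one McNemar variant should be chosen in advance, since the exact and uncorrected versions can differ (0.0625 v 0.025 in the example above). Exact McNemar cannot reach p < 0.05 with fewer than six discordant pairs (5 v 0 gives 0.0625).

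The cost is analysis wording only, with no extra patients, visits or data. The downsides are that the intervals are wide, cannot show equal recurrence, can disagree with the p-value at the margin in either cohort, and may need a short script if the named software does not offer them.

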### Study objectives and endpoints

The primary objective of this trial is to show that after TAPP repair for unilateral and bilateral inguinal hernias the acute postoperative pain caused by mesh fixation with tissue glue is less than with staple fixation.

The primary efficacy endpoint of the TISTA trial is pain under physical stress at 24 h after surgery. Pain will be rated by the patient using a numeric rating scale (NRS). The NRS ranges from 0 to 10 in steps of one, with 0 representing no pain at all and 10 the worst imaginable pain. The NRS is comparable to the visual analogue scale (VAS) where the degree of pain is marked on a 10 cm long line. In practical terms, average NRS and VAS scores (in cm) can be considered equivalent. The patient is first asked to rate the pain at rest and then to rate it after physical stress. Physical stress is induced by a 90° bending of the hip joint on the operated side(s). The secondary endpoints of the trial and their definitions are summarized in Table 
1.

**Table 1 T1:** Secondary endpoints and definitions

**Secondary endpoints**	**Definitions**
Pain rated before surgery and at 4, 8, 12, 36, 48 h after surgery	Measured on a numeric rating scale from 0-10 at rest and upon bending the hip joint on the operated side
Operating time	Time, in minutes, from the first skin incision to the application of dressing
Length of hospital stay	Time, in days (with one decimal precision), from start of surgery to hospital release
Postoperative analgesic requirements	Amount (g/day) and type (paracetamol, metamizole, morphine) of analgesic required after surgery, before hospital discharge
Incidence of persistent pain (neuralgia)	Neuralgia defined as:
	• The presence of intermittent hyperesthesia, burning sensation, or jabbing pain in the ipsilateral, inguinal area nerves (genitofemoral nerve, lateral cutaneous femoral nerve, ilioinguinal and iliohypogastric nerve) [20,22,27]
	• Evaluation will be performed 14 days, 1, 3 and 12 months after surgery
	• The degree of pain will measured as described above
Postoperative morbidity	Categorized according to Dindo et al [28], and it includes:
	• Wound infection, defined as infections treated without further surgery and identified by clinical examination without microbiological confirmation
	• Hematoma or seroma formation, identified by clinical examination alone, before discharge from hospital, which does not require radiological confirmation

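### Intermittently missing pain scores, including the 24 h primary score, are filled by single linear interpolation; this is unnecessary for the mixed model and can slightly bias the primary contrast if missingness or curvature differs between arms

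*Protocol article*

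**What the plan says.** Study objectives and endpoints: "The primary efficacy endpoint of the TISTA trial is pain under physical stress at 24 h after surgery". On the scale: "The NRS ranges from 0 to 10 in steps of one".

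Statistical analysis, primary test: "For the superiority analysis of pain intensity at 24 h after surgery, the Mann−Whitney U and Wilcoxon tests will be applied, as appropriate".

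Statistical analysis, longitudinal model: "Pain measurements performed at 4, 8, 12, 24, 36, 48 h after surgery", in both hernia groups, "will be analyzed in one mixed model to assess the mean ranks of the NRS scores".

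Statistical analysis, missing data: "Intermittent missing values will be replaced by linear interpolation (e.g. post-operative pain values within 48 h after surgery". The 24 h score lies in that window and is not exempted. Withdrawn patients fall under a separate rule in the same section.

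The article does not say in so many words that filled values are then treated like measured ones. That is an inference, but a fair one, since nothing distinguishes them in the analyses that follow.

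**The concern.** The article fixes this rule itself, so it can be assessed without the analysis plan. It has three weaknesses.

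- **Level.** A straight line between two points on a convex falling curve lies above the curve. If pain declines that way, a filled 24 h score is too high.
- **Information.** A filled row adds nothing that the patient's other scores do not already carry, yet the mixed model counts it as a further observation. A likelihood-based mixed model does not need the filling: it uses incomplete records as they are and is valid under missing-at-random.
- **Scale.** The average of two whole-number scores can be a half point, a value that no patient can give. This alters the ties in a rank test.

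What is at stake is the confirmatory 24 h comparison, if the level error differs between glue and staples, and to a lesser degree the standard errors of the longitudinal model.

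**Working it through.** **The plan's own figures.** They set the scale for any bias and they reproduce. Inputs from Sample size calculation: difference 1, SD 1, "two-sided analysis with a type I error of α = 0.05 and a power of (1-β) = 0.90".
- Two-sample t-test: power 0.8997 at 22 per arm and 0.912 at 23, so 23 per arm.
- Paired t-test with correlation 0.2: standardised difference 1/√(2 × (1 − 0.2)) = 0.791; power 0.885 at 18 and 0.903 at 19, so 19.
- Drop-out of 20%: 23/0.8 = 28.75, so 29; 19/0.8 = 23.75, so 24; 2 × 29 + 24 = 82.

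Nothing below changes these numbers.

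**Step 1: the filled value.** On the grid 4, 8, 12, 24, 36, 48 h, 24 h is midway between 12 h and 36 h. With both neighbours present, the filled score is (score at 12 h + score at 36 h)/2.

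**Step 2: error in one filled score.** Assume f(t) = 6 × 0.5^(t/h), with half-life h. The error is (f(12) + f(36))/2 − f(24).

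| h (hours) | f(12) | f(24) | f(36) | Error |
|---|---|---|---|---|
| 12 | 3.00 | 1.50 | 0.75 | 0.375 |
| 24 | 4.24 | 3.00 | 2.12 | 0.18 |
| 36 | 4.76 | 3.78 | 3.00 | 0.10 |
| 48 | 5.05 | 4.24 | 3.57 | 0.06 |

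The error is proportional to the assumed starting level.

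**Step 3: error in the treatment contrast.** Let m be the share of 24 h scores filled in an arm and b the error per filled score. The contrast is shifted by m₁b₁ − m₂b₂.
- Equal m and equal b: 0.
- 20% filled against 0%: 0.2 × 0.06 = 0.01 up to 0.2 × 0.375 = 0.075, so about 0.01 to 0.08 points.
- 10% against 0%: 0.006 to 0.038 points.
- Equal 20% filled, with half-lives of 12 h and 48 h in the two arms: 0.2 × (0.375 − 0.06) = 0.06 points.

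The 20% is illustrative. It is not the plan's drop-out allowance, which concerns something else.

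**Step 4: type I error of the primary test.** Simulation of the unilateral comparison: 23 per arm, SD 1, 20,000 runs, serial correlation 0.3 to 0.8 (assumed).
- Equal missingness of 10 to 20% and equal curvature: model SE 0.289 to 0.296, empirical SE 0.290 to 0.298, Mann-Whitney type I error 0.046 to 0.049.
- 20% filled against 0%, with b = 0.25 and 0.5: shift 0.05 and 0.10, type I error 0.048 and 0.060. The largest b in Step 2 (0.375) lies between these two.
- For comparison, b = 1.0 gives a shift of 0.20 and type I error 0.089, but no curve in Step 2 comes near that value.

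**Step 5: standard error of the mixed model.** Nominal SE with filled rows counted as data, against the true SE:

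| Assumed correlation | Missing | Nominal | True | Too small by |
|---|---|---|---|---|
| Exchangeable 0.3 | 10% | 0.1903 | 0.1935 | 1.7% |
| Exchangeable 0.3 | 20% | 0.1903 | 0.1962 | 3.0% |
| Exchangeable 0.6 | 20% | 0.2408 | 0.2436 | 1.1% |
| Autoregressive 0.6 | 20% | 0.2128 | 0.2138 | 0.5% |

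With observed scores only, the SE in these four cases is 0.1928, 0.1949, 0.2431 and 0.2138. That is no larger than the true SE with filling, so interpolation gains no precision.

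**The case against.** The strongest defence is that the rule is pre-specified, concerns only intermittent gaps, and does little harm. Much of this stands.

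- **Cancellation.** Patients and pain assessors are blinded, which makes arm-dependent gaps less likely. In bilateral patients a missed reading normally removes both sides' scores, so the level error cancels in the paired difference if curvature is similar.
- **Assumed curve.** The documents give no trajectory and no missing rate. Combined neuraxial and general anaesthesia could delay early pain, so smooth decay from the end of surgery is not established.
- **Unseen detail.** Sensitivity analyses may be in an analysis plan that is not shown. Their absence from the article is not the point here; the stated rule is.

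Two stronger readings are tempting, and the documents do not support them.

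A reader might infer that every standard error is too small, because the average of two readings with correlation ρ has only (1 + ρ)/2 of the variance of one reading (65 to 85% for ρ of 0.3 to 0.7). For the primary test this does not follow. Each filled value uses only that patient's own scores, so patients remain independent, and the test works with the variability actually present in the data. Step 4 shows no loss of type I error control when missingness and curvature are equal.

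A reader might also infer that earlier discharge in the glue arm, which the Discussion expects, carries the interpolation error into the contrast. A patient with no later score has a terminal gap. There is nothing to interpolate towards, and the rule does not cover that case.

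The defence does not show that interpolation is needed. It adds nothing to the mixed model, and for the primary score it rests on a straight-line assumption that can be avoided at little cost.

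**Conclusion.** The point holds as a modest weakness in a stated rule. A missing 24 h primary score with both neighbours present would be replaced by the 12 h/36 h average. Under convex decay from 6 points, that score is about 0.06 to 0.38 points too high. The glue-staple contrast moves only with a difference between arms in missingness or curvature: about 0.01 to 0.08 points at a 20-percentage-point imbalance in missingness, and nothing when both are equal. The article sets the benchmark: "We thus assumed a difference of 1 as a clinically relevant difference".

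The standard error of the primary rank test is not understated. That of the mixed model is about 0 to 3% too small at 10 to 20% missing. Decay shape, starting level, serial correlation and missing rate are all assumptions. The sample size of 82 is unaffected.

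**What to change.** 1. Delete the interpolation rule for the 4 to 48 h pain scores.
2. Fit the planned mixed model to all observed scores without imputation, and state that this relies on missing-at-random.
3. Keep the pre-specified Mann-Whitney and Wilcoxon tests for 24 h pain. Handle missing 24 h scores by one pre-specified multiple imputation from the patient's other time points and baseline, and state how the rank-test results are combined across imputations.
4. Report an observed-case analysis of the 24 h tests as sensitivity.

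The primary analysis should not switch to a model-based 24 h contrast only when 24 h scores turn out to be missing. That would let the data choose the confirmatory method.

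Cost: a change of analysis wording, a little more analysis work, and slightly wider intervals if scores are missing. Recruitment, data collection and sample size do not change.

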### Eligibility criteria and patient recruitment

Patients scheduled for elective laparoscopic primary inguinal hernia repair at the Department of Surgery, Kantonsspital St. Gallen, will be screened for enrollment in the trial. Informed consent will be obtained, at the latest, on the day before surgery, after ascertaining that the patient meets the eligibility criteria.

Patients that match the following criteria are eligible for inclusion in the clinical trial:

• age, 18 years or older

• male gender

• primary hernia repair (no re-operations for a recurrent hernia)

• no chronic pain

• no acute pain that requires analgesics, other than paracetamol or more than a single dose of non-steroidal anti-inflammatory drug treatment within 48 h before surgery

• no current treatment with psychopharmaceutical drugs

• good compliance can be expected

• no mental incapacity

• no known incompatibility (allergies) with Tisseel compounds

• informed consent

Under the following circumstances, patients will be excluded from the trial:

• hernia is inoperable with TAPP, due to the size, previous abdominal surgery (assuming a damaged peritoneum), or expected adhesions

• repair requires an intra-operative change to another hernia repair technique (e.g. open access methods)

• the patient wishes to stop further trial participation

When the patient refuses further participation after receiving surgery, the patient will receive a safety check-up during a one-month follow-up. Otherwise, the patient will not receive the study treatment and will not require a study-related safety follow-up.

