### Methods for reducing bias

The patients will be randomly assigned to the treatment, and the patients will be blinded to the assigned treatment. In primary arm 2 (patients with bilateral hernias), the bias of individual pain perception can be eliminated, because a single individual decides (blindly) which side is more painful.

The treatment assignment will be based on a block randomized list (one for each primary arm) with variable block sizes (between 2 and 6 patients per block). After each patient signed the informed consent, his name will be entered into the study database. At the beginning of surgery, the patients scheduled for unilateral repair will be examined laparoscopically to determine whether the other side also requires repair. The final decision for uni- or bilateral repair can only be made after this intra-operative examination. Thus, randomization will occur during surgery by contacting the study nurse to receive the treatment allocation. In the absence of the study nurse, the data manager can provide the allocation information. The data manager generates the randomization list and maintains a secured copy of the assignment list. The pain scores are obtained by nurses or physicians that are not aware of the treatment assignment (observer blinding).

In the case of unforeseen postoperative complications, the treating physician (surgeon) will know the treatment assignment and can be reached by phone. Furthermore, the data manager can unblind the assignment when necessary. Any unblinding will be recorded in the study documentation.

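### The confirmatory analysis is called intention-to-treat, but a patient converted to another repair technique after allocation would be dropped from it

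*Protocol article*

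**What the plan says.** The Statistical analysis section of the protocol article names the principle: "The confirmatory analysis will be performed based on an intention-to-treat (ITT) design, and it will adhere to ITT principles". The paragraph just before it sets a rule on whose data are used: "Data from patients withdrawn from the study will be disregarded, unless exclusion is based on a postoperative patient request". A second condition is attached to that exception: "and the patient agrees to the use of existing documented data". The per-protocol analysis is an addition: "When a protocol violation occurs, a per protocol analysis (PP) will be performed for comparison".

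The section Eligibility criteria and patient recruitment lists reasons for exclusion from the trial. Two of them can arise once the operation has begun: "repair requires an intra-operative change to another hernia repair technique (e.g. open access methods" and "the patient wishes to stop further trial participation".

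On timing, Methods for reducing bias explains that the choice between unilateral and bilateral repair is settled only at laparoscopy, and concludes: "Thus, randomization will occur during surgery by contacting the study nurse to receive the treatment allocation". The same section states that the surgeon knows the assignment.

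**The concern.** ITT means that every randomised patient is analysed in the group to which he was allocated. Here allocation falls in the middle of the operation, and one listed exclusion is an event that can occur later in the same operation. The rule on withdrawn patients speaks of withdrawal and exclusion as the same thing, so it reaches that event. Its only exception is a patient's own postoperative request, which a conversion is not.

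A person who knows the allocation takes the decision that removes the patient. If such removals differ between glue and staples, and the removed patients would have had more pain, the 24 h comparison no longer rests on the randomised groups. The same patients would also be missing from the morbidity and relapse comparisons.

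The loss may be permanent. The eligibility section gives a one-month safety check only to patients who refuse further participation after surgery, and states no study follow-up for the others. A 24 h score that was never taken cannot be restored by a later sensitivity analysis.

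**Working it through.** **1. The rules applied to each kind of patient**

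| Patient | Under the disregard rule | Under ITT | Conflict |
|---|---|---|---|
| Converted before the allocation call | out | never randomised | no |
| Converted after the allocation call | out (not a patient request) | in | **yes** |
| Withdrawn by the investigator after allocation for another reason (none is listed) | out | in | **yes, if it occurs** |
| Asks to stop after surgery, agrees to data use | in | in, with existing data | no |
| Asks to stop after surgery, refuses data use | out | consent limit | no breach |
| Other fixation used than allocated, repair remains TAPP | not a listed exclusion, so in | in | no |
| Postoperative complication | not a listed exclusion, so in | in | no |

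The per-protocol analysis is described as a separate comparison, so the disregard rule cannot be read as applying to that analysis alone.

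**2. The plan's own sample size (Sample size calculation)**

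Inputs: difference 1, SD 1, two-sided α 0.05, power 0.90, within-patient correlation 0.2, drop-out 20%.

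- Unilateral, two-sample t-test (noncentral t): power is 0.8997 with 22 per arm and 0.9125 with 23, so 23. Inflated: 23 / 0.8 = 28.75, so 29 per arm and 58 in all. This agrees with "Assuming a drop-out rate of 20%, the total number of patients needed per arm is 29".
- Bilateral, paired t-test: SD of the difference = √(2 × (1 − 0.2)) = 1.265. Power is 0.885 with 18 pairs and 0.903 with 19, so 19. Inflated: 19 / 0.8 = 23.75, so 24.
- Total: 58 + 24 = 82. The plan's figures reproduce.

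**3. How far exclusion could move a unilateral comparison (assumed values, not in the documents)**

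If k of 29 patients in one arm have pain D points above the rest and are dropped, the arm mean falls by (k / 29) × D. With k = 3 and D = 2, this is 3/29 × 2 = 0.21 NRS points, about a fifth of the target difference of 1. It assumes no offsetting loss in the other arm.

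**4. Effect on the type I error (simulation, same caveat)**

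Settings: 29 per arm, no treatment effect, Mann–Whitney test, rounded scores around 3 with SD 1, and in both arms a fraction f with D points more pain. There were 5,000 runs per setting (Monte Carlo standard error √(0.05 × 0.95 / 5000) ≈ 0.003).

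| f | D | Removed from one arm only | Removed from both arms |
|---|---|---|---|
| 10% | 1 | 0.059 | 0.050 |
| 10% | 2 | 0.082 | 0.051 |
| 20% | 1 | 0.093 | 0.044 |
| 20% | 2 | 0.171 | 0.049 |

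Equal removal leaves the error rate near nominal. Inflation comes from removal that differs by arm. The one-arm column is the extreme, in which every such patient leaves one arm and none leaves the other.

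**5. Bilateral patients**

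Excluding a bilateral patient removes both his glue side and his staple side. The within-patient contrast stays paired, so steps 3 and 4 do not apply to this stratum. The analysed set is still not all randomised patients.

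**The case against.** The strongest reply is that the exclusions may have been meant for patients who never reach study treatment. Allocation follows the laparoscopic look, so obstacles seen then can be settled before the call. The eligibility section also says that patients other than postoperative refusers do not receive the study treatment. This narrows the problem and may make the affected group very small. It does not remove the conflict: the conversion exclusion carries no time limit, and a patient allocated but not treated as allocated is still randomised.

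A reader might infer more than the text supports:

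- **That difficult fixation or complications lead to exclusion.** The trigger is a change to another hernia repair technique. Switching between glue and staples within TAPP, or bleeding after surgery, is not listed.
- **That the per-protocol set would be nearly identical to the ITT set.** Other protocol violations could leave the per-protocol set and stay in ITT. All that follows is that a converted patient, being in neither set, cannot be seen in the comparison.
- **That a fifth of the trial could be lost by this rule.** The 20% is a general drop-out allowance. Nothing ties it to conversions, and part of any withdrawal falls under the data-use exception.
- **That the whole primary comparison is biased.** The documents give no conversion rate and no sign of a difference between arms, and the bilateral pairing survives.

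**Conclusion.** The contradiction stands on the protocol's text alone. For a patient converted after allocation, or otherwise withdrawn by the investigator after allocation, the disregard rule and the ITT statement give opposite instructions. Two analysts could form different confirmatory sets, and each could cite the protocol.

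The size is unknown. The shift of about 0.2 points is a worst-case illustration that assumes 3 of 29 patients are lost from one unilateral arm, each with 2 points more pain, and none from the other. If exclusions are balanced between arms, the type I error is essentially unaffected. The point is therefore a wrongly fixed analysis set, and not a demonstrated bias. It should be settled while recruitment continues, because the scores have to be collected at the time.

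**What to change.** - Confine the disregard rule to patients excluded before allocation and to data whose use the patient refuses.
- Define the confirmatory set as all patients who received an allocation, analysed in the allocated arm or, for bilateral patients, by allocated side, whatever technique or fixation was finally used.
- In the eligibility section, limit the conversion exclusion to conversions decided before the allocation call. A later conversion removes the patient from the per-protocol set only.
- Keep recording the 24 h pain score and the later outcomes of converted patients.

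The cost is a few sentences and assessments for what are probably few patients. Converted patients dilute the contrast slightly: if 3 of 29 in one arm showed no effect of the allocated fixation, an expected difference of 1 would become 26/29 = 0.90. The sample size of 82 does not change. Should 24 h scores be obtained for all 29 per arm and all 24 pairs, power under the protocol's own t-test assumptions and before any such dilution would be about 96% in each stratum, against 91% and 90% with 23 per arm and 19 pairs.
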